#### Extension phase

An additional 36 participants will be recruited to the extension phase, and will be randomised on a 1:2 ratio to receive either:
Orally administered capecitabine alone 1000 mg/m^2^ twice a day (bd) or, capecitabine 850 or 1000 mg/m^2^ bd (as determined in the initial safety phase) plus radium-223 55 kBq/kg by i.v. injection on day 1 of cycle (2, 4, 6, 8, 10 and 12) of capecitabine for a total of six injections.

The sample size for the extension phase is based upon the primary toxicity endpoint of grade-III/IV toxicity. With 24 participants in the capecitabine plus radium-223 arm, this provides approximately 80% power to exclude a grade-III/IV diarrhoea rate of 25% from the upper limit of a one-sided 85% CI, assuming a rate of approximately 10% with capecitabine alone. If no more than 3/24 participants experience grade-III/IV diarrhoea the upper limit of the one-sided 85% CI will exclude 25%.

The control arm is included to provide concurrent standard of care data for interpretation only. No formal comparisons between arms will be made.

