### Study treatment

A maximum of 12 cycles of combination therapy is given unless disease progression or unacceptable toxicity are encountered. A cycle is 21 days in accordance with the standard administration of capecitabine.

A maximum of two doses of capecitabine are being investigated in this study; 850 mg/m^2^ bd and 1000 mg/m^2^ bd. The starting dose is 1000 mg/m^2^ bd which is in accordance with the standard administration of capecitabine. Capecitabine is delivered on days 4–17 for up to 12 cycles to provide a 3–4-day window before and after radium-223 to minimise any risk of potentiating normal tissue radiation sensitivity. After cycle 12, patients may continue with capecitabine off study as per standard of care, if they are continuing to receive clinical benefit.

Radium-223 is administered at 55 kBq/kg. This dose has been selected based on clinical data from previous studies in prostate cancer and breast cancer which have demonstrated efficacy and tolerability [14, 16–18]. Radium-223 is administered as a slow i.v. injection on day 1 of alternating cycles, starting at cycle 2 to provide one cycle of safety information in each participant with capecitabine alone.

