#### Initial safety phase

The safety data for the first cohort is reviewed by the Safety Review Committee and the capecitabine dose will either be expanded to a further three participants or de-escalated to 850 mg/m^2^ bd depending on the frequency and severity of toxicity experienced.

Toxicity data for each subsequent cohort is reviewed prior to dose expansion after three participants have been recruited and observed for DLTs, according to Fig. 3.

DLTs are assessed during the second cycle of capecitabine treatment up to the administration of cycle 3 day 1 and will be defined as the following events:
Gastrointestinal toxicity of ≥ grade III lasting > 48 h despite adequate supportive care measuresHaematological toxicity ≥ grade IV lasting > 7 days despite adequate supportive care measures which should exclude the use of bone marrow growth factors

Gastrointestinal toxicity ≥ grade III or haematological toxicity≥ grade IV experienced by participants during the first cycle, i.e. up to the administration of cycle 2 day 1 are not classed as DLTs as they are related to the capecitabine only.

The number of participants recruited to the initial safety phase, and the dose carried forward to the randomised extension phase is determined by the number of DLTs in line with the DLT schema.

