#### Evaluability

Participants can miss no more than 50% of doses in the first two treatment cycles in order to be evaluable for DLT in the initial safety phase. Participants missing more than 50% of doses for reasons other than toxicity without experiencing a DLT will be replaced.

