### Statistical analysis

Statistical analysis is the responsibility of the CARBON CTRU trial statistician. A full statistical analysis plan will be written before any formal analyses are undertaken.

During the initial safety phase, after every cohort of three participants, the CTRU trial statistician produces a summary of DLTs and AEs at each dose level, detailed safety listings and treatment compliance data for all participants in the study. The final analysis of primary endpoints and all secondary endpoints will take place when all participants have been followed up for at least 12 months.

The analysis population for the initial safety phase includes any participant who has received at least one complete cycle of capecitabine and radium-223. For the extension phase intention-to treat (ITT) population, per-protocol and safety analysis populations will be used. Statistical analysis is summarised by treatment arm.

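### DLT evaluability is judged on doses pooled over cycles 1 and 2, although DLTs can be counted only in cycle 2, so a participant with poor combination exposure can count as an evaluable non-DLT

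*Protocol article*

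**What the plan says.** The Evaluability section of the protocol article sets one exposure limit across two cycles: "Participants can miss no more than 50% of doses in the first two treatment cycles in order to be evaluable for DLT". The replacement rule follows: "Participants missing more than 50% of doses for reasons other than toxicity without experiencing a DLT will be replaced". Neither sentence sets a condition for cycle 2 alone or requires the radium-223 injection.

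The DLT window is narrower. The Initial safety phase section under Study treatment states "DLTs are assessed during the second cycle of capecitabine treatment up to the administration of cycle 3 day 1". Gastrointestinal and haematological toxicities of the qualifying grades "during the first cycle, i.e. up to the administration of cycle 2 day 1 are not classed as DLTs", because they are attributed to capecitabine alone. The Study treatment section explains why: radium-223 is given on alternating cycles, "starting at cycle 2 to provide one cycle of safety information in each participant with capecitabine alone". The Primary endpoint analysis likewise reports DLTs within the first cycle of radium-223.

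The Statistical analysis section defines the safety-phase analysis population by a different rule: "any participant who has received at least one complete cycle of capecitabine and radium-223".

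**The concern.** A DLT-evaluable participant should be one whose failure to have a DLT tells us something about the combination. Here a complete cycle 1, which cannot produce a DLT, can buy evaluability for a cycle 2 in which one component was omitted or hardly any treatment was taken. The rule also errs the other way: someone who missed cycle 1 but had almost all of the combination in cycle 2 is not evaluable.

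The DLT count determines the number recruited to the safety phase and the capecitabine dose carried into the randomised extension. With 6 to 12 evaluable participants, one or two uninformative non-DLTs matter, and they push towards declaring the combination safe.

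**Working it through.** The plan states no figure for this rule, so there is none to reproduce. The check is a dose count, followed by an illustration of the effect on the decision.

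**Inputs**
- "Capecitabine is delivered on days 4–17 for up to 12 cycles" (Study treatment): 14 days per cycle.
- Both capecitabine dose levels are given twice a day (Study treatment): 14 × 2 = 28 doses per cycle, 56 over cycles 1 and 2.
- One radium-223 injection falls in these two cycles (cycle 2 day 1): 56 + 1 = 57 doses if it is counted as a dose.
- Limit: at most 50% missed. This allows 28 missed doses on either count (28/56 = 50.0%; 28/57 = 49.1%).

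**Dose count under the pooled rule**

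| Cycle 1 | Cycle 2 | Missed, injection counted | Missed, capecitabine only | Evaluable? |
|---|---|---|---|---|
| Full | All capecitabine, no injection | 1/57 = 1.8% | 0/56 = 0% | Yes |
| Full | Injection, no capecitabine | 28/57 = 49.1% | 28/56 = 50.0% | Yes |
| Full | No injection, one capecitabine dose | 28/57 = 49.1% | 27/56 = 48.2% | Yes |
| Full | Nothing | 29/57 = 50.9% | 28/56 = 50.0% | Depends on the count |
| None | Injection, 27 of 28 capecitabine doses | 29/57 = 50.9% | 29/56 = 51.8% | No |

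**Would a per-cycle reading be enough?** Applying 50% to cycle 2 alone, with 29 doses including the injection, excludes the participant who took no cycle 2 capecitabine (28/29 = 96.6%). Omitting only the injection is 1/29 = 3.4%, so that participant stays evaluable. The injection needs its own condition.

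**Effect on the decision (illustration)**

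Assumptions: the dose passes with at most 1 DLT in 6 (the DLT schema in Fig. 3 is not shown); participants are independent; exposed participants have DLT probability p; unexposed participants have probability 0. With n exposed among the six,

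P(pass) = (1 − p)^n + n·p·(1 − p)^(n−1).

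At p = 0.35:
- n = 6: 0.0754 + 0.2437 = 0.319
- n = 5: 0.1160 + 0.3124 = 0.428
- n = 4: 0.1785 + 0.3845 = 0.563

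| True DLT rate | All six exposed | One unexposed | Two unexposed |
|---|---|---|---|
| 20% | 65.5% | 73.7% | 81.9% |
| 30% | 42.0% | 52.8% | 65.2% |
| 35% | 31.9% | 42.8% | 56.3% |
| 40% | 23.3% | 33.7% | 47.5% |
| 50% | 10.9% | 18.8% | 31.2% |

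**How far the zero-risk assumption matters.** Suppose a poorly exposed participant has a DLT probability of 10% instead of 0. The figure borrows the article's approximate grade III/IV diarrhoea rate on capecitabine alone, which is not a DLT rate, so it serves only to show scale. At p = 0.35:
- One such participant: 0.9 × 0.4284 + 0.1 × 0.1160 = 0.397
- Two: 0.81 × 0.5630 + 0.18 × 0.1785 = 0.488

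The rise from 31.9% is then to 39.7% and 48.8%, smaller but in the same direction.

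**The case against.** The case against has five parts.

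- **A reader might infer that these participants cannot have a DLT.** The article does not support that. A DLT is defined by type, grade, duration and window, with no requirement that radium-223 was given. A participant who missed only the injection still takes cycle 2 capecitabine, and one who took no cycle 2 capecitabine may have had the injection. This stands, and it makes the zero-risk probabilities upper bounds.
- **A reader might infer that a wholly untreated cycle 2 always counts as evaluable.** It does so only if the injection is not counted as a dose. This stands for that extreme case. The cases with one component missing do not depend on it.
- **The analysis population and the endpoint wording would drop the worst cases.** They may change the reported denominator. They are not linked to who counts in a cohort or who is replaced, so they leave two exposure rules for the same phase.
- **Compliance data are summarised after each cohort of three.** Low exposure would therefore be visible to the Safety Review Committee. Visibility helps, but the written rule still classes these participants as evaluable and gives no ground for replacing them.
- **This is a condensed article, and the limit may be meant per cycle.** The text does not say so, and a per-cycle limit would still not require the injection. The point concerns a rule the article states, not a missing detail.

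**Conclusion.** The concern holds. The stated evaluability window does not match the DLT window, and nothing requires the radium-223 injection. Given a full cycle 1, a participant can omit the injection, or all cycle 2 capecitabine, and still be counted as an evaluable non-DLT. A participant with near-complete combination exposure but a missed cycle 1 is not evaluable. The dose counts follow from the article alone.

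The direction of the distortion, towards passing the dose, is clear; its size is not. At a true rate of 35% the pass probability rises by at most about 11 percentage points with one unexposed participant (42.8 − 31.9 = 10.9) and 24 with two (56.3 − 31.9 = 24.4). This rests on the assumed at-most-1-in-6 rule, the assumed DLT rate and zero risk in the unexposed. The article gives no basis for how many of six would be poorly exposed, so these figures should not be read as the expected effect.

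**What to change.** Replace the pooled limit with a definition tied to the DLT window, keeping the protocol's own 50%:

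*A participant is evaluable for DLT if they had a DLT, or if they received the cycle 2 day 1 radium-223 injection, missed no more than 50% of cycle 2 capecitabine doses and were observed to cycle 3 day 1. Cycle 1 doses do not count. Participants who fall short of this for reasons other than toxicity, and who had no DLT, are replaced.*

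The toxicity exception must stay. Replacing someone who stopped cycle 2 treatment because of toxicity short of a DLT would itself make the dose look safer. The protocol should also say how such a participant is counted, since at present they are neither evaluable nor replaced.

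Reconcile the Evaluability and Statistical analysis sections so that the cohort decision and the reported DLT denominator use the same definition.

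The cost is a short change of wording and possibly one or two more replaced participants in the safety phase. No dose, schedule or DLT criterion changes.

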### Assessments

Participants are assessed clinically at baseline, on day 1 of each cycle, with additional haematology assessments during cycles 1 and 2 (days 8 and 15, respectively), at the end of study visit, and then at the 12-weekly follow-up visits.

Planar bone scintigraphy/SPECT ± computerised tomography (CT) is performed at baseline and at the end of study visit, and when clinically indicated. Chest/abdominal/pelvic CT or MRI is performed at baseline, weeks 12 and 24 after the initiation of treatment, at the of study visit and when clinically indicated.

Serum and second voided urine samples are collected to analyse changes in bone turnover markers at baseline, day 1 of alternating cycles starting at cycle 2, and at the end of the study visit.

Quality of life is assessed using EORTC QLQ-C30 and QLQ-Bone Metastases Module (QLQ-BM22) which will be completed by the participant prior to the first administration of trial treatment, day 1 of alternating cycles starting at cycle 2, and at the end of study visit.

Response is evaluated using RECIST v1.1 with comparisons to baseline evaluation.

### Data collection and management

All protocol-required information is completed at sites onto paper Case Report Forms by research staff, with the exception of quality-of-life information which will be completed directly by participants. Overall trial and data management is provided by the Leeds Clinical Trials Research Unit (CTRU), including monitoring of data for quality and completeness.

The independent Safety Review Committee (SRC) meets regularly to review the safety and ethics of the study by regularly reviewing the safety data during the dose escalation and expansion phases.

### Statistical analysis

Statistical analysis is the responsibility of the CARBON CTRU trial statistician. A full statistical analysis plan will be written before any formal analyses are undertaken.

During the initial safety phase, after every cohort of three participants, the CTRU trial statistician produces a summary of DLTs and AEs at each dose level, detailed safety listings and treatment compliance data for all participants in the study. The final analysis of primary endpoints and all secondary endpoints will take place when all participants have been followed up for at least 12 months.

The analysis population for the initial safety phase includes any participant who has received at least one complete cycle of capecitabine and radium-223. For the extension phase intention-to treat (ITT) population, per-protocol and safety analysis populations will be used. Statistical analysis is summarised by treatment arm.

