#### Initial safety phase

A minimum of six and a maximum of 12 evaluable participants will be recruited into the initial safety phase. This is based on the number of participants experiencing Dose Limiting Toxicities (DLTs), using a modified 3 + 3 approach (see Fig. 3).

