### Primary endpoint analysis

#### Dose Limiting Toxicities (initial safety phase)

The number of participants experiencing DLTs within the first cycle of radium-223 treatment will be presented, with descriptive summaries of the specific DLTs observed.

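### The safety-phase analysis population requires a complete combination cycle with no exception for a DLT, so on a strict reading it can omit a participant whose DLT cuts cycle 2 short, and it does not match the evaluability rule

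*Protocol article*

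**What the plan says.** The population is defined in the protocol article under Statistical analysis: "The analysis population for the initial safety phase includes any participant who has received at least one complete cycle of capecitabine and radium-223". No other route into the population is given.

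The timing comes from Study treatment. Radium-223 is given on day 1 of alternate cycles, "starting at cycle 2 to provide one cycle of safety information in each participant with capecitabine alone", and "Capecitabine is delivered on days 4–17 for up to 12 cycles". Under Initial safety phase in the same section, "DLTs are assessed during the second cycle of capecitabine treatment up to the administration of cycle 3 day 1"; toxicity in cycle 1 is expressly not a DLT because only capecitabine has been given by then.

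The Evaluability section sets a different rule. "Participants can miss no more than 50% of doses in the first two treatment cycles in order to be evaluable for DLT", and then: "Participants missing more than 50% of doses for reasons other than toxicity without experiencing a DLT will be replaced". The Sample size section uses the same term: "A minimum of six and a maximum of 12 evaluable participants will be recruited into the initial safety phase".

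The analysis itself is described under Dose Limiting Toxicities (initial safety phase): "The number of participants experiencing DLTs within the first cycle of radium-223 treatment will be presented". That section does not say which set of participants it draws on.

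**The concern.** A safety population should not depend on the participant getting through the period in which the safety event is counted. Here the qualifying condition and the DLT window fall in the same cycle. A gastrointestinal DLT is a severe toxicity lasting more than 48 hours, which can plausibly interrupt a 14-day oral course. If it does, the participant may fail the entry condition because of the event that the analysis is meant to count.

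Two things are at stake. The final DLT count could be too low, and the error can go only in that direction. The final table could also disagree with the cohort-by-cohort reviews, which appear to use the Evaluability rule. With 6 to 12 evaluable participants, one omission is visible.

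**Working it through.** The documents give no DLT rate or expected count, so there is no stated figure to reproduce. The check is mainly textual, with arithmetic to illustrate size.

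**Step 1: which cycle qualifies.** Radium-223 is first given on cycle 2 day 1, so cycle 2 is the first cycle with both drugs. The DLT window is cycle 2, closing at cycle 3 day 1. The two coincide.

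**Step 2: how many missed doses Evaluability allows.** Capecitabine on days 4 to 17 is 17 − 4 + 1 = 14 days, twice daily, so 28 doses per cycle and 56 over two cycles. The limit is 50%, or 28 missed doses. (I take doses to mean capecitabine doses, which the article does not specify.) A participant who took all of cycle 1 and stopped after day 9 of cycle 2 has taken 6 × 2 = 12 doses in cycle 2 and missed 16. That is 16/56 = 28.6%. This participant is evaluable under Evaluability, yet did not finish the cycle 2 course.

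**Step 3: the two rules side by side.** Each participant below took all of cycle 1 and received radium-223 on cycle 2 day 1. The strict reading takes a complete cycle to mean a combination cycle with its capecitabine course finished.

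| Participant | Statistical analysis, strict reading | Evaluability |
|---|---|---|
| DLT stops capecitabine in cycle 2; no later complete combination cycle | out | in |
| DLT starts after day 17, before cycle 3 day 1 | in | in |
| DLT interrupts cycle 2; a later combination cycle is completed | in | in |
| No DLT; some cycle 2 doses missed, within the 50% limit; no later complete combination cycle | out | in |

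Only the first row loses a DLT.

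**Step 4: looser readings.**
- If a complete capecitabine cycle (cycle 1 would do) plus one radium-223 injection is enough, all four rows are in and the bias goes. The sets still differ: a participant who missed a few doses in cycle 1 and then stopped for a DLT in cycle 2 has no complete capecitabine cycle, but can be within the 50% limit.
- If a cycle is complete once its 21 days have elapsed, DLT participants stay in. However, someone who missed more than 50% of doses for non-toxic reasons is also in, although Evaluability replaces that person.

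**Step 5: size on the strict reading.** With d DLTs in n participants, of whom k are omitted, the reported proportion is (d − k)/(n − k). The values of n, d and k are assumed.

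- 1/6 (16.7%) becomes 0/5 (0%).
- 2/6 (33.3%) becomes 1/5 (20.0%) or 0/4 (0%).
- 3/12 (25.0%) becomes 2/11 (18.2%), 1/10 (10.0%) or 0/9 (0%).

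In expectation, with true DLT probability p and a share q of DLTs that remove the participant, the reported proportion is p(1 − q)/[p(1 − q) + 1 − p]. Both p and q are assumed.

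| p | q = 0.25 | q = 0.5 | q = 0.75 | q = 1 |
|---|---|---|---|---|
| 0.20 | 15.8% | 11.1% | 5.9% | 0% |
| 0.33 | 27.0% | 19.8% | 11.0% | 0% |

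For example, with p = 0.20 and q = 0.5: 0.10/(0.10 + 0.80) = 11.1%.

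**The case against.** The strongest reply is that the exclusion rests on one reading of an undefined term. The article says that a cycle is 21 days, so complete may mean elapsed, and cycle 1 may count as the complete capecitabine cycle. On either reading a participant with a DLT is in, or almost always in. This stands as a limit on the size of the bias. It does not remove the mismatch with Evaluability (step 4), and the strict reading is the natural one for a phrase that joins the two drugs.

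Second, a reader might infer that every participant with a DLT is lost. The documents do not support that. Late-cycle DLTs are kept, and any later complete combination cycle also qualifies the participant.

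Third, a reader might infer that the capecitabine dose taken into the extension phase rests on a biased count. The documents do not support that either. The dose follows the number of DLTs under the DLT schema (figure not shown), recruitment is counted in evaluable participants, and the cohort safety listings and compliance data cover all participants.

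Fourth, the DLT section specifies a number of participants, not a rate. This is correct: the proportions in the working are illustrations. But the count falls too, for example from 2 to 1 or 0.

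Fifth, the first Evaluability sentence taken alone gives no exception for toxicity, so it could also exclude a participant with a DLT. This stands in part. By step 2, it bites only if more than 28 of the 56 doses over both cycles were missed, so someone who took all of cycle 1 is never caught by it. The replacement sentence then implies that a participant with a DLT counts. Because that is left to inference, Evaluability needs a clarifying sentence as well.

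A last defence is that the SAP would settle this. A SAP can add detail, but the article states a definition here, and that definition conflicts with another in the same document.

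**Conclusion.** The point holds in a limited form. The stated safety-phase population has no exception for a DLT and, read strictly, omits a participant whose DLT cuts cycle 2 short and who completes no later combination cycle. The final DLT count can then only be too low, and it could differ from the cohort reviews. The illustration of 2/6 falling to 1/5 or 0/4 rests on assumed counts and on the strict reading; on a looser reading the bias is small or absent. Under every reading considered, Statistical analysis and Evaluability define different sets, and the DLT section does not choose between them.

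This should be fixed before the final analysis. It affects how a primary safety result is reported; the documents do not show an effect on dose decisions.

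**What to change.** Replace the population sentence under Statistical analysis with one DLT-evaluable set: participants who received radium-223 on cycle 2 day 1 and who either (a) had a DLT in the defined window, up to cycle 3 day 1, whether or not the cycle was completed, or (b) met the existing Evaluability exposure rule.

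State under Evaluability and under Dose Limiting Toxicities (initial safety phase) that this set is used for both the cohort reviews and the final DLT table. Add to Evaluability that a participant with a DLT is evaluable whatever doses were missed.

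Two limits in this wording matter. DLTs must stay within the defined window, because the analysis counts only the first radium-223 cycle. The exposure rule must stay for participants without a DLT; otherwise someone who took very little treatment and stopped for other reasons would count as DLT-free and dilute the result.

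The cost is a few sentences in the protocol, carried into the SAP. No new data are needed, and no dose, DLT definition or other clinical rule changes.
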